**Figure 1 F1:**
[figure not shown]
The full protocol timeline for both the working time reduction intervention and control groups.

There have been two waves of data collection. An initial project to investigate the biological markers of working time reduction was initiated in 2022, with institutional funding. Subsequently, external grant funding supported a second wave of data collection (with no hiatus between the two waves). Data collection has been underway since March 2022, with control employers from 2025, except for a single control employer in 2022. We anticipate completing data collection in 2027. During this time, there have been minor changes to the protocol:

January 2023: The introduction of an optional 6-month follow-up (self-report questionnaires only). Therefore, this was not offered to the first seven employers.August 2023: Two additional questions were added to the sleep diary to record naps and whether they worked the previous day, alongside qualitative feedback from employees and business leaders at the end of the trial.September 2024: Four questions added to record information on job title, biological sex, self-reported height and weight to calculate BMI and current diet.

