### Participants and inclusion criteria

2.1

The study protocol was approved by the Brighton and Sussex Medical School Research Governance and Ethics Committee (RGEC; protocols ER/BSMS6337/4 and ER/BSMS6337/6) and conducted in accordance with the ethical standards set by the British Psychological Society and the Declaration of Helsinki. The study recruits two groups of participants: those undergoing working time reduction and control participants who do not change working hours.

We aim to recruit a balanced sample of at least 150 participants for all measures (with approximately half who reduce their working time and half controls). Sample size was determined using a power calculation in G^*^Power on questionnaire pilot data (*n* = 30) with an effect size of 0.45, alpha of 0.05 and power of 0.95. This suggests a group sample size of at least 68 is required. Furthermore, participation in certain study components is voluntary (e.g., MRI, blood sample, interoception, sleep, and time-use diaries), and therefore sample sizes are expected to vary across modalities as a consequence of participant self-selection and differential uptake of specific measures; accordingly, statistical power is also expected to vary between outcome domains. However, as this is the first working time reduction trial to use non-self-report measures, it was not possible to estimate power calculations beyond questionnaire data. In addition, as we will not examine moderating subgroup effects within the control group, fewer controls may be required. The primary purpose of the control group is to account for factors unrelated to the intervention itself, including practice effects, familiarity with the MRI scanning environment, and temporal changes that may occur irrespective of working time reduction. This will allow us to determine whether observed changes in outcomes can be attributed to the working time reduction intervention rather than repeated testing or assessment effects.

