### Recruitment

2.3

Employers have been recruited on a rolling basis between 2022 and 2026. Unlike most national cohort-based working-time-reduction trials, this protocol requires local recruitment because several core measures, including MRI scans, blood samples, and interoception measures, must be conducted in person at the University of Sussex. As only a minority of staff at each organization volunteer for in-person testing, a large pool of local employers is needed to achieve adequate sample sizes on these measures. Therefore, we prioritize organizations based near the research site, and invite them to join the trial at a time that suits their operational needs. Recruitment for both control and working time reduction participants is supported through local business newsletters, community talks by the senior researcher ([name]), public engagement events, research participation bulletins, social media posts, and word of mouth. A small number of employers participating in UK national pilots coordinated by the 4 Day Week Foundation have also opted into the protocol, alongside the national programmes.

Employers are primarily contacted through a senior decision-maker (e.g., CEO, Managing Director, or Human Resources lead), who determines whether their staff will implement working-time reduction or serve as controls. Except for one organization that contributed to both groups, all employees within a given organization are assigned to the same group. Organization leaders inform staff about the study and, where applicable, the planned reduction in working time. Staff are invited to a discovery call with the senior researcher, after which they can opt into the study and select which components they wish to complete (i.e., questionnaires only, additional remote measures, or an in-person visit). Participation in the research is voluntary and independent of eligibility to take part in time management training (see Section 2.5) and, for the working time reduction group, participating in their employer's working time reduction trial.

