### Model design

3.2

This study uses a longitudinal mixed-effects design with a hierarchical structure. Repeated measures data are nested within employees, who are nested within companies, meaning observations are not independent and will be analyzed using multilevel methods. The design includes one between-subjects factor (group: intervention and control) and one within-subjects factor (time, which will vary per analysis with three datapoint options: baseline and end of trial; baseline, end of trial and 6-month follow-up; and the weekly questionnaires), with an interaction between time and group and corrections for multiple tests. When relevant, employee-level (e.g., age, household income) and company-level (e.g., industry, company size) covariates will be added to statistical models. Table 1 provides a list of all planned covariates. The independent variables will be fixed effects, with up to three random effects: time, employee, and organization. Covariates will be added to the model as fixed effects. This design enables us to determine whether changes are observed across time points for the working time reduction intervention group but not for controls.

**Table 1 T1:** Planned individual-level and company-level covariates for inclusion in statistical models.

Category	Covariate	Type
Individual-level	Baseline value of dependent variable	Continuous
	Gender or sex	Categorical
	Household income	Categorical
	Education level	Categorical
	Age	Continuous
	Living area	Continuous
	Job title	Categorical
	Hours of working time reduction	Continuous
	Remote work status	Categorical
Company-level	Industry	Categorical
	Company size	Categorical
	Trial start month	Categorical
	Profit status	Categorical

The specific coding scheme used for categorical variables alongside any data specific covariates will be specified in future modality-specific preregistrations.

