This protocol also addresses several limitations common in previous trials. Firstly, data collection spans multiple years (2022–2027), with employers initiating the research protocol at different times of the year. This rolling recruitment approach helps to reduce the influence of seasonal effects that may arise when data for all participants are collected on the same schedule. For instance, the non-profit 4 Day Week Global coordinated trials in which multiple employers were studied on the same calendar timeline, with a coordinated switch date to the new schedule, and cohort-level work reorganization support (Backmann et al., 2024; Fan et al., 2025; Gomes and Fontinha, 2024).

Secondly, control groups have not always been included in working time reduction studies (e.g., Lewis et al., 2023), or have used much smaller sample sizes than working time reduction groups (e.g., Backmann et al., 2024; Fan et al., 2025), or do not receive the same organizational training that enables isolation of changes due to working time reduction specifically (e.g., Fan et al., 2025). In contrast, our study includes a balanced control group of comparable size and sector composition, whereby control organizations complete the same protocols. This includes time management training, which allows stronger causal inference by isolating the specific effects of reduced working time from changes attributable to advice on productivity and time-management principles.

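### Controls date almost entirely from 2025 while data collection began in 2022, and the primary model as written has no term that could remove a period difference in change from the group-by-time effect

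*Protocol article*

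**What the plan says.** Section 2.3: "Employers have been recruited on a rolling basis between 2022 and 2026". The employer's decision-maker chooses the group, so nothing balances calendar time between groups. Section 2.6 gives the timeline: "Data collection has been underway since March 2022, with control employers from 2025, except for a single control employer in 2022", and "We anticipate completing data collection in 2027".

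Section 2.1 lists what the control group is there to account for, including "temporal changes that may occur irrespective of working time reduction". The Discussion adds, on season: "This rolling recruitment approach helps to reduce the influence of seasonal effects". Its limitations paragraph covers self-selection, expectancy and blinding, but not the different calendar spans of the two groups.

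Section 3.2 sets out group, time and their interaction, with up to three random effects, and then says: "Covariates will be added to the model as fixed effects". Table 1 is presented as the full list of planned covariates. Its only calendar item is "Trial start month", categorical and at company level. Whether this means month of the year or month and year is not stated. Interaction terms beyond group by time are planned for secondary moderator analyses, with extent of reduction, sex, age and baseline score named.

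Section 2.6 also records a change in September 2024: "Four questions added to record information on job title, biological sex, self-reported height and weight to calculate BMI and current diet". Job title is nevertheless a Table 1 covariate.

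**The concern.** A control group removes temporal change only if it is observed over the same period. From March 2022 to the end of 2024 there is one control employer. If change over a 14-week protocol differed between those years and 2025 onward, for example because working conditions or study procedures shifted, that difference is counted as an effect of working time reduction. It could act in either direction. Because group by time is the primary contrast for every data type, each modality inherits the problem.

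The covariate list looks as if it deals with calendar time, but a start-month term that is constant within a person does not act on the change being tested. The same timeline means that items added in September 2024 are missing mainly in the intervention group. A whole-sample model with job title would either drop the early intervention participants or impute their values from later ones.

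**Working it through.** The plan gives no figure on this point, so there is none to reproduce. The only design figure used below is the planning effect size of 0.45 (Section 2.1), as a yardstick. Its standardising SD is not stated.

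**1. Why a main effect cancels.** For person i with group g and a covariate x that is constant within the person:

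- baseline: y0 = a + b·g + γ·x + e0
- end of trial: y1 = a + b·g + c + d·g + γ·x + e1
- change: y1 − y0 = c + d·g + (e1 − e0)

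γ·x drops out. With complete two-wave data, d is the same with or without x. A random time effect does not help, because it takes deviations in change to average zero within each group, which a period imbalance violates.

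**2. Size of the bias.** Let change differ by δ between pre-2025 and later starts, and let p1 and p0 be the pre-2025 shares of the intervention and control groups. Then bias in d = (p1 − p0)·δ. The documents give no counts by year, so p1 = 0.60 and p0 = 0.05 are assumptions:

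| δ (SD) | bias = 0.55 × δ | as share of 0.45 |
|---|---|---|
| 0.1 | 0.055 | 12% |
| 0.2 | 0.11 | 24% |
| 0.4 | 0.22 | 49% |

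The bias is proportional to the gap in shares. Half the gap (27.5 points) gives half the bias, 0.0275 to 0.11 SD. If years differ only in level and not in change, δ = 0 and there is no bias.

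**3. Simulation check.** 150 people in 30 companies of 5, two time points, no true effect, 300 datasets. Intervention starts were spread evenly over 2022 to 2026 (60% before 2025); 1 of 15 control employers started before 2025; δ = 0.2 SD. The formula predicts (0.60 − 1/15) × 0.2 = 0.107.

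| Model | mean spurious effect (SD) | SD of estimate |
|---|---|---|
| group × time | 0.110 | 0.165 |
| + start quarter, main effect | 0.110 | 0.165 |
| + start quarter × time | 0.103 | 0.198 |
| + start quarter × time and period × time | −0.007 | 0.230 |

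The first two models agreed within 5e-15 in every dataset. The same identity held in 20 fits with a random intercept per person.

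**4. What adjustment costs.** Take 75 per group with the same assumed shares and ignore clustering. Information on a group contrast is n1·n0/(n1 + n0).

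- Unadjusted: 75 × 75/150 = 37.5
- Before 2025: 45 × 3.75/48.75 = 3.46
- From 2025: 30 × 71.25/101.25 = 21.11
- Period-adjusted: 3.46 + 21.11 = 24.57, so the standard error rises by √(37.5/24.57) = 1.24
- From 2025 only: standard error rises by √(37.5/21.11) = 1.33

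**The case against.** The strongest reply is that the model is being read too literally. Adding covariates as fixed effects contrasts with the random effects named just before; it does not exclude covariate-by-time terms. Coding, moderators and additional covariates are left to later preregistrations. This stands as a caution: main effect only is a reading of the text, not a statement in it. But Section 3 offers this plan as common to all data types, and calendar confounding is common to them too, so the shared plan is the place to settle it.

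A reader might infer several stronger claims that the documents do not support:

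- **The covariates adjust nothing.** Too absolute. Table 1 includes the baseline value. If end-of-trial scores were analysed given baseline, main-effect covariates would adjust the group effect, though month of the year would still not adjust for year. With incomplete data a main effect can also move the estimate slightly, and the numerical check covers complete two-wave data only.
- **The plan adjusts for month but not year.** The meaning of start month is open. If it means month and year, it still cancels as a main effect. Interacted with time, most 2022 to 2024 levels would have no control employer.
- **Season is confounded with group.** Nothing shows different seasonal mixes. Controls from 2025 can cover every season.
- **Every item added in September 2024 damages the adjustment.** Table 1 already allows gender or sex, and BMI and diet are not in it.

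Practice effects and scanner familiarity, also given as reasons for controls, depend little on calendar overlap. Section 2.2 and its neighbours speak mainly of employers; the few independent participants in Section 2.3 are undated, so the pre-2025 control share may not be exactly one employer's staff.

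**Conclusion.** The point holds in this form. The recruitment timeline leaves 2022 to 2024 with essentially no concurrent control, the protocol relies on the controls to account for temporal change, and it does not list the gap as a limitation. The primary model as written would not remove a period difference in change from a complete two-wave group-by-time estimate. That follows from algebra and needs no assumption about size.

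The size is not known. The 0.055 to 0.22 SD range, 12% to 49% of the planning effect, rests on an assumed 60%/5% split and an assumed drift of 0.1 to 0.4 SD. It shows what is possible, not that the trial is biased by that amount. No document reports a period difference in change.

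**What to change.** These are changes to the analysis plan, and data collection is expected to run to 2027, so they can be made before the final analysis.

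1. Pre-specify a concurrent comparison limited to employers starting from 2025 in both groups. Report it beside the full-sample result, and rest any claim to have excluded temporal change on it.
2. In the full-sample model, add calendar period (before 2025, from 2025) by time. State that its pre-2025 part rests on one control employer.
3. Enter start season and the few key company-level covariates as covariate-by-time terms, and define start month.
4. Add the non-concurrent controls to the limitations, and qualify the statements in Section 2.1 and the Discussion about temporal and seasonal change.
5. Do not use job title as a whole-sample covariate. Use gender rather than the later-added sex item in whole-sample models.

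The cost is precision. The concurrent comparison has fewer intervention participants, and the added terms use degrees of freedom, so the list should stay short. Under the assumed split the standard error rises by about 24% with period by time and 33% in the concurrent comparison. The true cost depends on how many intervention employers start from 2025, which the document does not give. Early intervention data remain usable for within-group questions such as extent of reduction.

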### Measures

2.7

The following sections describe the broad method and implementation model for each measure. There are four key data collection points: baseline, trial, end-of-trial, and 6-month follow-up. For all sections below, we collect identical data at the start and end of the trial, except for the “Work Patterns Questionnaire.” As shown in Figure 1, the “Weekly Goals and Questionnaires” are collected weekly from baseline week 1 through trial week 12 (i.e., over 14 weeks) and again at the 6-month follow-up. The “Workplace and Wellbeing Questionnaires” are collected once during baseline weeks 1 and 2, at the end of the trial (week 12), and at the 6-month follow-up. The “Work Patterns Questionnaire” is collected only in the last trial week (i.e., trial week 12). Data for the three opt-in remote measures, time-use diaries, sleep diaries, and sleep watches are collected during baseline weeks 1 and 2 and again at the end of the trial during trial weeks 10 and 11 (sleep watches and diaries), or week 11 (time-use diaries). For the three opt-in in-person visit measures at the University of Sussex, blood samples, MRI scans, and the body perception measure are collected in weeks 1 and 12 of the trial period. For working time reduction participants, the in-person measures are scheduled for the time they would otherwise have spent working during weeks 1 and 12.

### Questionnaires

2.8

#### Weekly performance: goal attainment

2.8.1

On the first day of each participant's working week, participants are emailed and asked to set five work-related goals for that week (based on Uhlig et al., 2023). Participants are told that these goals can be main tasks or responsibilities that they want to achieve by the end of their work week. Using Qualtrics (Provo, UT), participants then rate the extent to which they met their goals on their last working day of that week as part of the “Weekly Questionnaires” described below. Ratings are made on a five-point scale ranging from 1 (not at all) to 5 (goal met in its entirety), adapted from Harris et al. (2003) to measure goal attainment on a weekly basis. Participants are also given the option to respond with 0 if they did not set a goal. We do not record the goals set; instead, we ask participants to keep their own records to help evaluate whether they met them.

#### Weekly questionnaire

2.8.2

On the last day of a participant's working week, they complete a battery of questionnaires on Qualtrics, including the weekly goal attainment evaluation from Section 2.8.1 and the following seven measures. Unless participants are taking leave for a full working week, they are still asked to complete the questionnaires, even if they work only 1 day.

**Positive and negative affect schedule (PANAS)**: A 20-item scale assessing positive and negative affect (Watson et al., 1988). Respondents rate 10 positive and 10 negative adjectives on a five-point scale based on how they have felt over the past week, from 1 (very slightly) to 5 (extremely). Positive and negative affect scores are summed separately, with higher scores indicating greater positive or negative affect.

**Maslach burnout inventory (MBI)**: A 22-item scale measuring burnout across three subscales: emotional exhaustion, depersonalization, and personal accomplishment (Maslach et al., 1996). Participants reflect on how much a statement applies to them over the past week. For example, “I feel emotionally drained by my work.” Responses use a seven-point scale from 1 (not at all) to 7 (completely). Scores on the emotional exhaustion scale range from 1 to 63, and on the depersonalization scale from 1 to 35, with higher scores indicating more severe burnout. Scores on the personal accomplishment scale range from 1 to 56, with lower scores indicating more severe burnout.

**Recovery experience questionnaire**: A four-item questionnaire assessing psychological detachment from work. Participants evaluate how much a statement applies to them over the past week (Sonnentag and Fritz, 2007). For example, “I forgot about work.” Responses are given on a five-point scale from 1 (I do not agree at all) to 5 (I fully agree), with higher scores indicating increased psychological detachment from work.

**Work engagement questionnaire**: A nine-item questionnaire evaluating how participants feel at work (Schaufeli et al., 2006). Participants rate the extent to which a statement reflects how they feel about their work in the past week on a six-point scale from 0 (never) to 6 (always). For example, “At my work, I feel bursting with energy,” with higher scores indicating a more positive work-related state of fulfillment.

**Task performance questionnaire**: A seven-item subscale of employee performance on in-role behavior from the job satisfaction and organization commitment questionnaire (Williams and Anderson, 1991). Ratings are given on a five-point scale, from 1 (strongly agree) to 5 (strongly disagree), reflecting on the past week at work. Although the original questionnaire's scale ranges from 1 (strongly disagree) to 5 (strongly agree), we reversed the response options to encourage participants to actively think about their response, by changing the format of the scale between questionnaires. The first five items are reverse coded, so that higher scores indicate better task performance. The seven statements selected are:

Adequately completed my assigned duties.Fulfilled responsibilities specified in my job description.Performed tasks that are expected of me.Met the formal performance requirements of the job.Engaged in activities that will directly affect my performance evaluation.Neglected aspects of the job that I am expected to perform.Failed to perform my expected duties.

**Pittsburgh sleep quality index (PSQI)**: A single modified question from the 19-item PSQI to measure sleep quality over the last week, rather than a month: “During the past *week*, how would you rate your sleep quality overall?” on a four-point scale from 0 (very good) to 3 (very bad). A higher score indicates poorer sleep quality (Buysse et al., 1989).

**Adherence check**: To assess whether participants are following their intended working time, participants in the working time reduction group are asked whether they worked on their fifth free day, “On your 4-day week work-free day, did you do any work? This includes engaging in work communications, such as email or phone calls.” with four possible responses: not at all, some of the day, most of the day, and all of the day. If participants indicate they worked on their work-free day, we ask an open-ended follow-up question as to why. Those who followed a 9-day fortnight are presented with the same two questions to check whether they worked, with “4-day week work-free day” replaced by “9-day fortnight work-free day.”

Participants in the control group have an alternative phrasing for this question, given that they do not have a fifth free day: “*Over the course of the past working week, please indicate the extent to which you were undertaking work during your contracted hours each day (including work communications such as emails or phone calls). Please select the option that best reflects your engagement for the average working day this week*.” Responses use the same 1–4 scale as for working time reduction participants, but with some additional detail on the amount of work undertaken: (1) Not at all [Undertook no work during contracted hours], (2) Some of the day [Worked for less than half of contracted hours], (3) Most of the day [Worked for more than half of contracted hours], and (4) All of the day [Fully engaged in work for all contracted hours].

**Annual leave check**: Initially, we only checked leave taken during the trial in the “Work Patterns Questionnaire” at the end of the trial (see Section 2.8.5); however, participants reported difficulty remembering all leave taken (e.g., half days for medical appointments). Therefore, in July 2024 we introduced an additional question to the “Weekly Questionnaire” to check any leave taken during the working week just experienced. We do not record the reason, only the time taken.

